### Eligibility criteria

The study population consists of adult patients (> 18 years old) that are approved for cochlear implantation according to standard care criteria. Patients will initially undergo a series of diagnostic tests to assess eligibility for cochlear implantation. These are as follows: a CT scan, a pure tone audiogram/speech test, psychological evaluation, and a consultation by the audiologist and ENT specialist. The Cochlear Implant Team of the UMC Utrecht will assess the work-up results and assess eligibility for cochlear implantation, according to the current clinically applied criteria.

All cochlear implant models will be included in this study. The choice for the cochlear implant model lies with the patient and the CI team of the UMC Utrecht and will not be affected by taking part in this trial. In order to be eligible to participate in this study, a participant must have provided written informed consent authorization before participating in the study. They also must have Dutch written language proficiency and be physically able to undergo a CBCT scan.

A potential participant who is a revision or reimplantation candidate, is unable to understand or sign informed consent, or is pregnant during the trial will be excluded from participation in this study.

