### Outcomes

At intake, demographic data will be extracted from the electronic patient database: age, gender, if the deafness is pre- or postlingual, and electronic address. The following outcomes will be assessed at the baseline visit and follow-up visits at 1, 4, and 8 weeks and at 3 and 12 months postoperatively (Fig. 2). All measurements will be performed by the research team following the same protocol procedures.

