##### Speech perception

Three months and 1 year after cochlear implantation, a conventional speech perception test with/without noise test will be performed with CVC words from the “Nederlandse Vereniging voor Audiologie” (NVA) word-list. Each list contains 11 words with a total of 33 phonemes. This is according to regular care. The speech tests can be quantified with a simple correct percentage score in bimodal solution if the patient has a hearing aid in the contralateral ear.

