### Sample size

This sample size calculation was based on the primary outcome, R/S migration after 12 months. Due to limited quality evidence on the migration rate for both techniques, an estimation of the migration rates cannot be based on literature; therefore, we base our assumptions on clinical expertise [34, 42, 43]. We consider a migration under 1.0 mm or 1° to be clinically irrelevant. Migration under these cut-off points is within the measurement error margin of the measurement technique of the CBCT scan analysis. A sample size of 51 per study arm reaches 80% power (*β* = 0.8) and a significance level (*α*) of 0.05 with a non-inferiority margin of 1.0 mm. Standard deviation is estimated at 2.0 mm based on the database of Maxwell et al. [43]. In order to cover for possible loss to follow-up estimated at a maximum of 10%, we will include 56 patients per study arm.

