### Randomization and blinding

Patients will be randomly assigned to one of the two study groups with 56 patients allocated in each group. Randomization takes place in the UMC Utrecht-endorsed electronic data capture system Castor EDC. (https://www.castoredc.com/). After giving informed consent, patients will be randomized with an allocation ratio of 1:1 and variable block sizes, with stratification for age (18–50 years, >50 years). Stratification is applied in both study groups. This is a single-blind study, meaning that only participants are blinded for the treatment allocation. The randomization will be done before surgery and patients will not be informed about the allocation. The research team is not blinded. The outcome data will be blindly analyzed. Blinding of the data will be performed by the electronic Case Report Form system used (see section “Data collection plan”). In the event that a revision surgery is necessary for removal or repositioning of the CI, unblinding is permitted. A member of the research team will inform the subject of the allocation.

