#### Statistical analysis secondary objectives

COMPASS questionnaire scores between intervention and control at 3 and 12 months after cochlear implantation will be calculated using the unpaired *t*-test (or the Mann-Whitney *U* test).

Statistical analysis of electrode migration data will be compared in a number of cases and percentages. To calculate any association between electrode migration of ≥ 1 mm and R/S device migration, and between electrode migration and a decrease in speech performance tests, Pearson’s correlation test or a Spearman rank correlation test will be performed. Electrode impedance values will be compared between the groups with the unpaired *t*-test (or the Mann-Whitney *U* test). CVC word score tests (with and without noise) will be compared between the groups with the unpaired *t*-test. Within-group comparisons will be calculated with differences of mean values. A clinically relevant speech performance decrease is a speech performance test score decrease of ≥ 7% when scoring between 30 and 80%, and ≥ 5% when the patients’ scores < 30 or > 80% on the speech performance test, a definition based on clinical experts. Incidence and degree of complications will be reported by means of frequencies.

Participants who withdraw from the study prematurely will be considered lost and will be replaced. Reasons for withdrawal or premature termination will be documented. Potential missing data will be handled using multiple imputation. Complete case analyses will be performed as a sensitivity analysis. All analyses will be performed on an intention-to-treat basis.

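### The between-arm comparison of CVC speech scores uses an unadjusted t-test, leaving out the age stratum and the onset of deafness already recorded at intake: valid, but less precise than it could be

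*Protocol article*

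**What the plan says.** In the protocol article, under Statistical analysis secondary objectives: "CVC word score tests (with and without noise) will be compared between the groups with the unpaired" t-test. The sentence names no covariate, change score or stratum term. The section adds only within-group differences of means and a threshold for a relevant drop in an individual's score.

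The outcome is scheduled under Speech perception: "Three months and 1 year after cochlear implantation, a conventional speech perception test with/without noise test will be performed with CVC words".

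Three baseline items could bear on it:

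- **Age.** Randomization and blinding describes 1:1 allocation in variable blocks "with stratification for age (18–50 years, >50 years").
- **Onset of deafness.** Under Outcomes, the data extracted at intake are "age, gender, if the deafness is pre- or postlingual, and electronic address".
- **A preoperative speech test.** Eligibility criteria says "Patients will initially undergo a series of diagnostic tests to assess eligibility for cochlear implantation", and lists "a CT scan, a pure tone audiogram/speech test, psychological evaluation, and a consultation by the audiologist and ENT specialist".

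None of the three appears in the speech analysis.

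**The concern.** The trial takes adult primary implant candidates whether their deafness began before or after language was acquired, and allows all implant models. Speech scores after implantation can therefore be expected to vary between patients for reasons unrelated to how the receiver/stimulator is fixed. Whatever part of that variation age and onset of deafness explain stays in the error term of a plain t-test, although both are known before surgery.

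Two things follow. The confidence interval for the speech difference is wider than the collected data allow. And the stratification is not carried into the analysis: if age predicts the score, balancing the arms on age while leaving age out of the model makes the t-test somewhat conservative.

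The sample size was set for device migration only, so precision on speech depends entirely on how the scores are analysed. This concerns a method that the article states, not a detail left to a document that is not shown.

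**Working it through.** **The plan's own figure.** The only sample size in the article is for migration: "A sample size of 51 per study arm reaches 80% power" at a level "of 0.05 with a non-inferiority margin of 1.0 mm", with an SD of 2.0 mm. The standardised margin is 1.0/2.0 = 0.5 SD. With a true difference of zero and a one-sided 5% test, the exact non-central t gives 79.9% power at 50 per arm and 80.6% at 51, so 51 reproduces. (At one-sided 2.5%, 51 per arm would give 70.6%.) No power, SD or target difference is stated for speech, so this figure serves here only as the evaluable number per arm.

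**Inputs for the speech comparison**

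- n = 51 per arm (Sample size).
- Significance at p < 0.05 (Statistical analysis), taken as two-sided: an assumption.
- Multiple correlation rho between the covariates and the CVC score: not in the documents, so shown as a range.
- True difference: not in the documents. It is set at the value that the unadjusted test detects with 80% power, purely as a reference point.

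**Step 1: reference difference.** Non-centrality = d × sqrt(n/2), degrees of freedom = 2 × 51 − 2 = 100. Solving for 80% power gives d = 0.560 SD.

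**Step 2: effect of adjustment.** The residual SD is SD × sqrt(1 − rho²), so the standardised difference becomes 0.560/sqrt(1 − rho²).

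| rho | Residual variance, 1 − rho² | Adjusted d | Power | Equivalent unadjusted n per arm, 51/(1 − rho²) |
|---|---|---|---|---|
| 0 | 1.00 | 0.560 | 80.0% | 51 |
| 0.2 | 0.96 | 0.572 | 81.6% | 53 |
| 0.3 | 0.91 | 0.587 | 83.6% | 56 |
| 0.4 | 0.84 | 0.611 | 86.4% | 61 |
| 0.5 | 0.75 | 0.647 | 89.9% | 68 |

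The power column charges one degree of freedom for adjustment. Charging three instead changes power by less than 0.02 percentage points.

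**Step 3: in score units.** For an assumed SD of 20 percentage points, the difference detectable with 80% power is 0.560 × 20 = 11.2 points unadjusted. Multiplying by sqrt(1 − rho²) gives 11.0 points at rho 0.2, 10.7 at 0.3, 10.3 at 0.4 and 9.7 at 0.5.

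**Step 4: which covariates the article supports.** Age and onset of deafness are in the intake list, and age is also the stratum. The preoperative speech score is not in that list. The eligibility work-up names a speech test without saying that it uses the CVC list, or giving the ear, aid or noise condition. The Data collection plan has the team extract the clinical parameters it needs from the health records. The score may therefore be obtainable, but the article does not show that it is trial data.

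**The case against.** The strongest reply is that nothing here is wrong. An unpaired t-test on randomised arms is valid, speech is a secondary outcome with no power claim, and covariate adjustment is often settled in the analysis plan. The first two parts stand: this is a loss of efficiency, not an error. The third has less force, because the article does not stay silent; it names the test.

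The gain is also unproven, and that stands. No correlation, speech SD or share of prelingual patients is given, and the 0.56 SD reference difference is a device of the calculation. If the covariates predict little (rho 0.2), the gain is under 2 percentage points of power.

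Three stronger readings are tempting, and the documents do not support them:

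- **That a preoperative speech score is at hand for every patient, so that adjusting for it is only a change of wording.** The article shows a speech test in the work-up but not its type or its entry as trial data. Candidates with severe to profound loss may also score near the floor, which would limit its value as a covariate.
- **That a chance imbalance in onset of deafness would bias the result.** Under randomisation, the error rate of the t-test already allows for such imbalance. Adjustment improves precision and removes the effect of an observed imbalance from the estimate; it does not rescue an invalid test.
- **That speech is the trial's formal check that the pocket technique does not cost hearing.** The article attaches no non-inferiority or safety claim to speech. It is one listed secondary outcome.

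**Conclusion.** The point holds as a minor, optional improvement. The stated analysis of CVC scores is valid but leaves out the randomisation stratum and a recorded characteristic that plausibly predicts the outcome. The cost is precision only: from 80% power unadjusted, adjustment would reach about 82% to 90% for a multiple correlation of 0.2 to 0.5. Those figures assume 51 evaluable patients per arm, a two-sided 5% test, a true difference of 0.56 SD and a linear relation between covariates and score. None of the correlations comes from the documents. The direction needs only that the covariates predict the score to some degree; if they do not, adjustment loses next to nothing.

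**What to change.** In Statistical analysis secondary objectives, replace the t-test for CVC scores by a linear model, fitted at 3 and at 12 months, with arm, age stratum (18–50, over 50) and pre-/postlingual deafness. Report the adjusted difference between arms with its 95% confidence interval, and keep the unadjusted t-test as a sensitivity analysis. Fix this before the outcome data are analysed.

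Add the preoperative speech score as a further covariate only if it can be extracted from the health records under a comparable test condition across patients. It need not be on the same scale as the outcome, but the condition must be defined first.

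The core change needs no new visit, test or patient. It costs two degrees of freedom, or three with the preoperative score, which would also require some data definition and extraction.

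### The 7- and 5-point cut-offs for a relevant speech decrease lie within the chance variation of 33-phoneme lists; if that class is what is correlated with electrode migration, the association is pulled towards zero

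*Protocol article*

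**What the plan says.** Under Speech perception, the protocol article describes the material: "Each list contains 11 words with a total of 33 phonemes". On timing it says: "Three months and 1 year after cochlear implantation, a conventional speech perception test with/without noise test will be performed". On scoring: "The speech tests can be quantified with a simple correct percentage score". It does not state how many lists are presented per occasion and condition.

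Under Statistical analysis secondary objectives, a Pearson or Spearman correlation is planned "between electrode migration and a decrease in speech performance tests". Later in the same paragraph comes the definition: "A clinically relevant speech performance decrease is a speech performance test score decrease of" at least "7% when scoring between 30 and 80" per cent, and at least "5% when the patients’ scores" lie below 30 or above 80%. The stated basis is "a definition based on clinical experts"; no test-retest error is given. The paragraph does not say whether the correlation uses this class or the numerical change in score.

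Electrode migration is itself a yes/no outcome in the section of that name: displacement of the basal electrode by 1 mm or more.

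**The concern.** A rule that labels individual patients as worse has to be judged against how far a score moves when nothing has changed. A percentage score from 33 items moves a good deal between two tests. For the primary outcome, the article sets its cut-off against a measurement error margin (Primary outcome measure; Sample size). The speech cut-off gets no such check.

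At stake is the secondary question of whether electrode migration goes with loss of speech performance. If many patients classed as decreased are in fact stable, and this happens equally in migrated and non-migrated patients, the observed association shrinks. A null result could then be taken as reassurance that electrode migration does not harm hearing.

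**Working it through.** The article gives no error rate for the speech cut-offs, so there is no stated figure to reproduce.

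**Inputs from the article.** 33 phonemes per list; scores as percentage correct at 3 and 12 months; cut-offs of 7 points (30-80%) and 5 points (otherwise), read as percentage points.

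**Assumptions.** The 3-month score is the reference. The true proportion *p* is the same on both occasions. Phonemes are independent. The number of lists *L* is varied because it is not stated.

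**Step 1: cut-offs in phonemes.** One phoneme = 100/33 = 3.03 points. With one list, a drop of at least 7 points means at least 3 phonemes (9.1 points), and a drop of at least 5 points means at least 2 phonemes (6.1 points).

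**Step 2: chance SD of a difference.** SD = 100 × √(2p(1−p)/n), with n = 33.

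- p = 0.5: √(0.5/33) gives 12.3 points; 7/12.3 = 0.57 SD.
- p = 0.8: √(0.32/33) gives 9.8 points; 7/9.8 = 0.71 SD.
- p = 0.2: also 9.8 points; 5/9.8 = 0.51 SD.
- p = 0.9: √(0.18/33) gives 7.4 points; 5/7.4 = 0.68 SD.
- p = 0.95: √(0.095/33) gives 5.4 points; 5/5.4 = 0.93 SD.

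**Step 3: share of unchanged patients classed as decreased.** This is the exact sum of P(X₁ = i) × P(X₂ = j) over all pairs in which the drop meets the rule. X₁ and X₂ are independent binomials with n = 33*L* and proportion *p*, and the cut-off is chosen by the first score.

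| True score | 1 list (33) | 2 lists (66) | 4 lists (132) |
|---|---|---|---|
| 10% | 0.27 | 0.15 | 0.09 |
| 20% | 0.31 | 0.22 | 0.16 |
| 50% | 0.27 | 0.22 | 0.12 |
| 80% | 0.30 | 0.21 | 0.15 |
| 90% | 0.27 | 0.15 | 0.09 |
| 95% | 0.19 | 0.08 | 0.03 |

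Over true scores of 10-95% the ranges are 19-31%, 8-22% and 3-16%; three lists give 7-21%. The normal approximation for one list agrees: 0.28 at 50% and 0.25 at 90%.

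**Step 4: sensitivity to the assumptions.**

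- With a true gain of 5 points from 50%, the rates fall to 15% (one list), 9% (two) and 2% (four).
- Correlation between phonemes of the same word would raise the rates; the article gives nothing from which to quantify this.
- If one list is scored by whole words (11 items), the rates are 28-42%.

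**Step 5: effect on the association, as illustration only.** Assume that 10-20% of electrodes migrate, that half of the migrated patients truly decline and no others do, and that the rule catches 90% of true declines. Write *m* for the share migrated, *a* and *b* for the shares classed as decreased with and without migration, and π = ma + (1−m)b. Then φ = (a−b)√(m(1−m)) / √(π(1−π)).

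- No misclassification: a = 0.5, b = 0, so φ = 0.69 (m = 0.1) or 0.67 (m = 0.2).
- 25% false decreases: a = 0.5 × 0.9 + 0.5 × 0.25 = 0.575 and b = 0.25, so φ = 0.22 (m = 0.1) or 0.28 (m = 0.2).

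**The case against.** The strongest objection is that the text does not tie the cut-off to the correlation. The definition comes several sentences after it, and Pearson and Spearman suit a continuous change. If the continuous change is meant, the analysis proposed here is largely the one already planned. This stands as a limit: the dilution is conditional. The classified reading remains the more natural one, because the definition has no other stated use, and one sentence would settle it.

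Second, the size depends on the number of lists, which a journal article may leave to the full protocol, and on no true change between 3 and 12 months. Both are correct, so the result is given as a range and not as a single share.

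Third, clinical relevance is not the same as statistical detectability, and experts may set a relevant change below the noise of the test. That is fair for group means. For labelling individual patients, the noise decides what the label is worth.

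Two stronger readings are tempting and are not supported:

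- A reader might infer that a per-arm frequency of speech decrease will be reported and will be mostly noise. No such analysis is planned. Counts and percentages are named for electrode migration and frequencies for complications, while speech is compared between arms by t-test on the scores.
- A reader might infer that the expert rule must give way to a 95% critical difference. That is a trade-off and not a correction. At a 50% score the critical difference is about 24 points with one list and 17 with two. For a true fall from 60% to 45%, it would flag 26% of patients against 73% under the article's rule with one list, and 39% against 83% with two.

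**Conclusion.** The concern holds in a limited form. Both cut-offs are below one SD of the chance difference between two single-list scores, across true scores from 10 to 95%. An unchanged patient is classed as decreased with a probability of about 19-31% (one list), 8-22% (two) or 3-16% (four), assuming independent phonemes and no true change. If this class enters the correlation, the association with electrode migration is biased towards zero, the more so because migration is also cut, at 1 mm. The drop in φ shown above depends on assumed prevalences and indicates direction and rough size only.

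The point concerns one secondary association. The primary outcome, the sample size and the between-arm comparison of mean speech scores do not depend on it.

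**What to change.** In Statistical analysis secondary objectives, state that the association is tested with the continuous change in speech score from 3 to 12 months against electrode displacement in mm, using the Spearman test already named. Keep the 5-7% class as descriptive only. Report it with the number of phonemes presented per occasion and the share of unchanged patients expected to meet it by chance.

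The cost is wording: the scores and the scans are already being collected. The continuous change carries the same measurement noise, so some attenuation remains, but no further information is lost by cutting both variables. The result is also less easily told as a proportion of patients who got worse, and the descriptive class still serves that purpose.

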## Background

### Background and rationale

Cochlear implants (CIs) provide hearing through direct electrical stimulation of the auditory nerve in patients with sensorineural hearing loss and have become standard care for adult and pediatric patients with severe to profound bilateral hearing loss. Cochlear implantation surgery requires careful planning and execution. The correct electrode array positioning in the cochlea is crucial for optimal functionality of the device. This array is connected to the body of the implant, known as the receiver/stimulator (R/S) device. During cochlear implantation, the R/S device is placed and fixated on the skull. It should be placed close to the pinna, without possible interference of the microphone in the behind-the-ear device laying (partially) on top of the R/S device.

The standard fixation technique of the R/S device, which is recommended by the surgeon’s guide that is supplied with the respective implants, consists of drilling out a part of the bony cortex of the skull (a bony recess), as well as non-absorbable suture retaining holes [1]. The bony recess technique lowers the profile of the R/S device in relation to the skull surface and holds it in place with non-absorbable sutures to the bone. Although rare, complications that are due to drilling of the bony recess can have serious consequences. Depending on the extent of drilling and the cortex thickness of the patient, the dura mater is sometimes exposed [2, 3]. Several studies report on dural tears with subsequent cerebrospinal fluid leakage as a direct result of extensive cortical drilling [4–6]. Other complications that have been reported (but occur very rarely) and associated with this technique are late-onset hematomas, epi-/subdural hematoma, tentorial herniation, and cerebral infarction, as well as meningitis [5, 7–11]. To avoid such risks, in recent years ENT surgeons have adopted less invasive techniques [1–3, 10, 12–20]. Additionally, later CI models have a lower profile and a flatter bottom. However, the lowering of the profile is a trade-off for a larger footprint which results in a larger bony recess thus a larger area of the skull is drilled out.

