#### Objectives

The primary objective of our study is to compare the migration rates of the two fixation techniques (bony recess vs. subperiosteal tight pocket) by analyzing 3D reconstructions of the R/S device, acquired by cone-beam computed tomography (CBCT) scans at baseline and at 3 and 12 months post-surgery. Secondary objectives are to investigate the difference between the two fixation techniques in patient-experienced burden using the validated COMPASS questionnaire, electrode array migration rate, and electrode impedance values. Other secondary objectives are to investigate the association of electrode impedance values with R/S device and electrode migration, and whether complaints of performance drop, vertigo, tinnitus, headache, or nonauditory stimulation are associated with electrode array migration and R/S device migration. We will also compare the complication rate of these surgical techniques, for major and minor complications. Finally, we will validate the measurement method technique with flexible tape measure for the assessment of migration of the R/S device [35].

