#### Secondary outcome measures

##### Electrode migration

Electrode array migration is defined as a displacement of the basal electrode outside the cochlea of ≥ 1 mm (i.e., approx. 1 contact spacing). To compare the electrode array migration rate between the two surgical techniques, we will analyze the acquired CBCT scan images following a previously validated method [29, 37]. Electrodes, situated at the level of the round window, will be categorized as extracochlear, since electrodes at this position do not provide adequate stimulation or accurate pitch perception so that they mostly have to be removed from the stimulation map.

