##### Complications

Incidence and degree of complications according to the following categories:

Device failure, which is classified into hard or soft failure using standardized criteria described in the 2005 Cochlear Implant Soft Failures Consensus Development Conference Statement [39].Major and minor complications according to the proposal of Hansen et al. [40].◦Major: a significant medical problem (e.g., meningitis), additional major surgery (e.g., cholesteatoma surgery or reimplantation due to a patient-related problem), explantation of the device for any reason other than device-related failure, any degree of permanent disability (e.g., facial nerve paralysis)◦Minor: complications leading to extended hospitalization or treatment on an outpatient basis, complications settling spontaneously or by conservative medical treatment, and complications managed by a minor surgical procedure (e.g., simple hematoma aspiration by syringe).

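### Electrode migration and complication rates are to be compared between techniques, but the stated between-arm method gives only counts, percentages or frequencies, with no effect estimate or interval (minor, secondary outcomes only)

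*Protocol article*

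**What the plan says.** Two secondary aims of the protocol article are comparisons between techniques. Under Objectives: "We will also compare the complication rate of these surgical techniques, for major and minor complications". The same section lists the difference in electrode array migration rate, and the outcome definition under Electrode migration repeats the aim: "To compare the electrode array migration rate between the two surgical techniques". That outcome is binary, a displacement of at least 1 mm.

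The section Statistical analysis secondary objectives then states the method. For electrode migration: "Statistical analysis of electrode migration data will be compared in a number of cases and percentages". For complications: "Incidence and degree of complications will be reported by means of frequencies". The latter matches the outcome definition under Complications, "Incidence and degree of complications according to the following categories", which covers device failure and major and minor events.

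The section also introduces an analysis with "To calculate any association between electrode migration of" 1 mm or more and two other variables, R/S device migration and a fall in speech score. That relates outcomes to one another, not to treatment arm. COMPASS scores, impedance values and CVC scores each have a named between-arm test. Missing data are to be multiply imputed, and "Complete case analyses will be performed as a sensitivity analysis".

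**The concern.** The aim is a comparison, and the stated method ends at two columns of counts. A reader sees how many patients in each arm had an event, but not the estimated difference or how large a true difference the data still allow.

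This matters because safety is part of the trial's rationale. The Discussion says that the safety of the pocket technique is not yet established with certainty. If both arms show a handful of major complications, or none, the table alone can look like evidence of equal safety when a difference of several percentage points remains possible. The primary analysis of R/S device migration, its margin and the sample size are not affected.

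**Working it through.** **Inputs from the article (Sample size).** 51 evaluable patients per arm; 56 per arm randomized to allow for up to 10% loss; primary outcome margin 1.0 mm, SD 2.0 mm, 80% power, alpha 0.05.

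**The plan's own figure.** With one-sided alpha 0.05 (the article does not state the sidedness) and a true difference of 0, n = 2 × (1.645 + 0.842)² × 2.0² / 1.0² = 49.5, so 50 per arm by normal approximation. With the noncentral t distribution, power is 79.9% at 50 and 80.6% at 51, so 51 reproduces. For dropout, 50/0.9 rounds up to 56 and 51/0.9 to 57; the stated 56 is within rounding. Both 51 and 56 are used below.

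**Assumed.** Event counts. The article gives no expected rate for electrode migration or for complications.

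**Formula.** Newcombe 95% interval for a difference d = p1 − p2. For each arm take the Wilson limits

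l, u = [p + z²/2n ∓ z√(p(1−p)/n + z²/4n²)] / (1 + z²/n), with z = 1.96.

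Then lower = d − √[(p1−l1)² + (u2−p2)²] and upper = d + √[(u1−p1)² + (p2−l2)²].

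**Two cases in full, 51 per arm.**
- 0 v 0: l = 0 and u = 3.8416/(51 + 3.8416) = 0.0700, so the interval is ±7.0 points.
- 5 v 5: p = 0.0980, l = 0.0426, u = 0.2098; √(0.0554² + 0.1117²) = 0.1247, so the interval is ±12.5 points.

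**Equal counts (difference 0), 95% interval in percentage points.**

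| Events in each arm | 51 per arm | 56 per arm |
|---|---|---|
| 0 | ±7.0 | ±6.4 |
| 1 | ±8.5 | ±7.8 |
| 2 | ±9.7 | ±8.9 |
| 3 | ±10.8 | ±9.9 |
| 5 | ±12.5 | ±11.5 |

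**Unequal counts.**

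| Events | 51 per arm | 56 per arm |
|---|---|---|
| 3 v 0 | +5.9 (−2.1 to +15.9) | +5.4 (−2.0 to +14.6) |
| 4 v 0 | +7.8 (−0.6 to +18.5) | +7.1 (−0.6 to +17.0) |
| 5 v 0 | +9.8 (+0.9 to +21.0) | +8.9 (+0.8 to +19.3) |
| 5 v 2 | +5.9 (−4.9 to +17.4) | +5.4 (−4.6 to +16.0) |

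Against no events in the other arm, the interval first excludes zero at 5 events.

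**If electrode migration is not rare.** The simple half-width 1.96 × √(2p(1−p)/n) is 11.6 (n = 51) or 11.1 (n = 56) points at an assumed 10% in both arms, and 15.5 or 14.8 points at 20%. The imprecision in absolute terms then grows.

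**Why an interval and not a test.** By normal approximation, power is 16 to 17% for 5% v 10% and 29 to 32% for 10% v 20%. With no events in one arm, Fisher's exact test needs 6 in the other to reach p < 0.05. A non-significant result would say little; an interval shows what remains possible.

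**The case against.** The strongest reply is that this is analysis-plan detail. The article condenses a fuller protocol, a separate analysis plan may add intervals, and neither sentence says that only tables will be given. Frequency tables of complications are standard, side-by-side percentages are a comparison of a kind, and a reader can derive an interval from counts and denominators. Nor do the named tests for the other secondary outcomes come with a stated interval.

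Much of this stands, and it keeps the point small. It does not remove it. The article is not silent on these two outcomes: it states a between-arm method for each, and that method gives neither an effect estimate nor a measure of precision for a declared comparison.

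Three stronger readings are tempting, and the document does not support them.
- A reader might infer that low counts are to be expected for all these outcomes. The Background says "Although rare, complications that are due to drilling of the bony recess can have serious consequences", but that covers only complications of drilling. It does not cover minor complications in general, and for electrode migration the same Background section suggests that it happens more often than was once believed.
- A reader might infer that the investigators intend to claim equal safety from similar tables. Nothing in the article says so, and no stated decision rests on these tables.
- A reader might infer that the frequency tables are an error or contradict the objectives. They are not wrong; they are incomplete for a comparison.

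**Conclusion.** The point holds as a minor improvement to secondary outcomes. The objectives call for a between-technique comparison of electrode migration and of major and minor complications, and the method stated for it carries no estimate of the difference and no interval. With equal counts of 0 to 5 per arm, the 95% interval is about ±6 to ±13 percentage points at 51 to 56 per arm, so similar tables would not show similar safety.

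The size rests on assumed counts, on complete data for 51 or 56 patients per arm, and on the Newcombe method. It does not depend on events being rare: at higher rates the intervals are wider still.

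**What to change.** Keep both existing sentences and the frequency tables of incidence and degree of complications, including device failure. Add to Statistical analysis secondary objectives:

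*The proportions of patients with electrode migration of at least 1 mm, with at least one major complication and with at least one minor complication by 12 months will also be compared between arms as a risk difference with a 95% confidence interval (Newcombe on observed data, and the pooled equivalent where multiple imputation is used). These comparisons are secondary, and absence of a difference will not be read as equal safety.*

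The interval should not be confined to complete cases, because the article makes that analysis a sensitivity analysis. The technical form of the pooled interval can be left to the analysis plan.

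Cost: one added sentence, with no new data, visits or patients, and nothing now reported is lost. The downside is that wide intervals make any safety statement visibly weaker.
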